### Overarching project

2.2

This study is part of the ERANET‐NEURON consortium ‘Microbiome Gut‐Brain interaction in Anorexia Nervosa’ (MiGBAN) which aims to investigate the gut‐brain interaction in adolescent and adult patients with AN and in animal models by means of longitudinal studies and randomized‐controlled trials. The overarching MiGBAN project is coordinated by the Department of Child and Adolescent Psychiatry, Psychosomatics and Psychotherapy, RWTH Aachen University, Germany. Another interventional study with a parallel study design will be conducted by the RWTH University of Aachen which will investigate the effect of supplementation of omega‐3 poly‐unsaturated fatty acids (PUFA) instead of probiotics in adolescents with AN.

### Study design and recruitment

2.3

The present study is a two‐centre, longitudinal, double‐blind, randomised, placebo‐controlled trial (RCT) comparing the clinical efficacy of administration of probiotics (in addition to TAU) compared with placebo in 60 patients with AN. TAU consists of psychiatric/psychotherapeutic inpatient treatment with nutritional rehabilitation aimed at the restoration of a healthy weight and starting a psychotherapeutic process (details on TAU with outcome data can be found in Mairhofer et al. [2021]). It is important to include inpatients only, as nutritional rehabilitation needs supervision and very detailed reporting of food, fluid and probiotics/placebo intake. Outcome data will be compared to 60 sex‐ and age‐matched healthy controls who will be followed for one year but do not receive any intervention. The sample of healthy controls will serve as a baseline for a general comparison of the MI and other variables of interest between patients with AN and healthy controls. The study design is summarised in Figure 1. Hospitalised patients with AN will mainly be recruited from the Medical University of Vienna (Department of Child and Adolescent Psychiatry, Eating Disorders Unit) and additionally from the Medical University of Innsbruck (Department of Child and Adolescent Psychiatry. Healthy controls will be recruited from the Vienna study site and the German cooperation/coordination site at RWTH‐Aachen University via flyers, posters and social media.

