### Storing and processing of blood and stool samples

2.9

Blood serum samples will undergo centrifugation and are separated into aliquots of 500 µl and stored at −80°C. Analysis for inflammatory markers, gut permeability markers and hormones will be conducted using ELISAs.

For the collection of stool samples the patient is instructed to line the toilet bowl with toilet paper before defecation to guarantee an accurate sample collection. Further, they are instructed to put three pea‐sized amounts of stool with the spoon, which is attached to the stool tube, into the tube and then to cap the tube.

After collection, the stool samples will be sent to the Biobank, divided into three aliquots and frozen at −80°C as fast as possible (usually within 24 h). For follow‐up assessments and healthy control subjects, stool tubes are sent by post or provided at an appointment at the clinic. They are instructed to collect the stool sample at home and bring it to their appointment at the clinic. The stool sample is then stored within 48 h.

In order to analyse the MI composition frozen stool samples collected from patients and HC will be subject to microbial genomic DNA extraction. Briefly, total DNA will be extracted using the QIAamp PowerFecal DNA Kit (Qiagen), following the manufacturer's protocol. The V3‐V4 region of the 16S rRNA gene will be amplified and sequenced on an MiSeq Illumina sequencer. Raw reads will be quality checked using FastQC v0.11.6 (Andrews et al., 2015). QIIME2 will be used to process and analyse the sequence data (Bolyen et al., 2019). Paired end sequences will be denoised by using dada2 (Callahan et al., 2016), and clustered into amplicon sequences variants (ASVs) using ‘vsearch’ with an identity of 0.97 (Rognes et al., 2016). Bacterial ASVs will be annotated using q2‐feature‐classifier plugin (Bokulich et al., 2014). The ASV table will be read into R v3.2.3 for statistical investigation with the vegan package (Dixon, 2003).

Blood and stool samples are stored at BIOBANK General Hospital of Vienna and BIOBANK of the Medical University of Innsbruck. All samples will be labelled with study pseudonyms containing the respective measurement time point and dates of sampling.

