### Statistical analysis plan

2.13

The primary analysis will be based on the intention‐to‐treat principle (ITT), including all randomized patients irrespective of the amount of treatment actually received. A per‐protocol analysis will be performed as sensitivity analysis. In order to follow ITT principle as closely as possible, all participants will be asked to participate in the end‐of‐treatment and follow‐up assessment (at 6 months and 1 year), in particular regarding BMI measurement, even if they drop out of treatment, to minimise the amount of missing data.

We will test for a difference in the primary outcome measure (age‐adjusted BMI at 1 year follow‐up) between the probiotics and placebo arm using a mixed‐effects model repeated measures analysis with covariates study site, sex, atypical/typical AN, and BMI at admission and will include any available further measurements of BMI (in particular at discharge and month 6). As this is equivalent to a phase II trial, emphasis will be on the 95% confidence intervals of the effect size estimates; additionally, *p*‐values will be calculated.

Secondary outcomes such as eating disorder pathology and changes in the gut MI will be analysed in a similar way, additionally using measures of MI community composition and diversity measures, mostly in a descriptive way.

In addition to the randomized comparison between probiotics and placebo groups, a comparison between healthy controls and patients (in both arms) will be done to assess both differences in gut MI composition and diversity between patients with AN and healthy controls in the most acute phase of disease (at admission to inpatient treatment) and to assess the size of changes during and after treatment and weight rehabilitation in patients with AN compared to natural fluctuations of MI composition in healthy adolescents during normal development. Again, mixed‐effects models repeated measures analyses with an emphasis on descriptive reporting of confidence intervals of effect sizes will be performed.

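### Stool is handled differently in patients and controls, and the patients' route changes during the trial, so handling can imitate or mask normalisation of the microbiome

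*Protocol article*

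**What the plan says.** **Handling (section 2.9).** The general instruction is that stool goes to the biobank and is frozen at −80°C "as fast as possible (usually within" 24 h). A separate instruction covers follow-up assessments and healthy controls: "They are instructed to collect the stool sample at home and bring it to their appointment at the clinic", with storage within 48 h. The text does not say whether those 48 h run from collection or from the appointment. Samples are labelled with time point and date of sampling; clock times are not mentioned.

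**Visits (sections 2.5 and 2.8, Table 1).** Patients give stool at admission (T_A), discharge (T_D), 6 months (T_6) and 12 months (T_12). Controls have no discharge visit. T_D is dropped when T_6 falls close to discharge. Sections 2.1 and 2.13 treat 6 months and 1 year as the follow-up times.

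**Analysis (section 2.13).** Beyond the randomised comparison, "a comparison between healthy controls and patients (in both arms) will be done". It covers composition and diversity at admission, and the size of the patients' changes set against natural fluctuation in controls. It uses mixed models and emphasises confidence intervals.

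**Centres (section 2.3).** "Hospitalised patients with AN will mainly be recruited from the Medical University of Vienna", "and additionally from the Medical University of Innsbruck". For controls: "Healthy controls will be recruited from the Vienna study site and the German cooperation/coordination site at" Aachen. Controls are matched on sex and age.

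**The concern.** Controls are on the home route at every visit. Patients are on the inpatient route at T_A and, on a natural reading, at T_D, and then move to the home route. Handling is therefore aligned with group at admission and with visit within patients. If holding time or transport alters the measured composition, part of the admission difference is handling, and part of the later change in patients is the change of route.

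At stake is the reading of patients against healthy adolescents over time. The Discussion presents this as a strength of the study, and the Conclusions in the abstract speak of normalising the microbiome. An analysis plan can add covariates later, but it cannot separate handling from disease unless the times were recorded and overlap between the groups.

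**Working it through.** The plan gives no figure for this, so the check sets out the design and then shows how an assumed effect would pass through it.

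**Route by group and visit (sections 2.5 and 2.9)**

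| | T_A | T_D | T_6 | T_12 |
|---|---|---|---|---|
| Patients | inpatient, usually 24 h | inpatient (natural reading) | home, 48 h, unless still in hospital | home, 48 h |
| Controls | home, 48 h | not assessed | home, 48 h | home, 48 h |

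**Algebra.** Let D be the true patient-minus-control gap, held constant, and h the shift of the home route relative to the inpatient route.

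- Observed gap at T_A: D − h.
- Observed gap at T_6 and T_12: D.
- Spurious change in the gap: D − (D − h) = h.
- If a share p of patients is still in hospital at T_6, the spurious change at T_6 is (1 − p)h.
- T_A to T_D in patients: same route at both visits, so h cancels.
- Probiotics against placebo: both arms switch alike, so h cancels.

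**Size, under assumptions.** Take 60 against 60 and one feature in SD units, with D = 0, p = 0 and within-person correlation 0.5. The standard error of the admission contrast is √(2/60) = 0.183. The SD of a within-person change is √(2(1 − 0.5)) = 1, so the change contrast has the same standard error. The chance that a 95% interval excludes zero is P(|Z + h/0.183| > 1.96):

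| h (SD) | h/0.183 | Formula | Simulated, admission | Simulated, change |
|---|---|---|---|---|
| 0 | 0 | 5% | 5.1% | 5.5% |
| 0.2 | 1.10 | 19% | 21% | 20% |
| 0.3 | 1.64 | 38% | 38% | 38% |
| 0.5 | 2.74 | 78% | 77% | 78% |

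The simulation used 4,000 runs per row. In the same runs the probiotics-placebo change contrast stayed near 5%.

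**Direction.** The gap appears to move from |D − h| to |D|.

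- D = 0: an apparent gap of |h| at admission that disappears later.
- D = −0.5, h = +0.5: from 1.0 to 0.5, apparent normalisation.
- D = −0.5, h = −0.5: from 0 to 0.5, a hidden admission gap followed by apparent divergence.
- Shift orthogonal to the disease difference, both 0.5: from √(0.5² + 0.5²) = 0.71 to 0.50, apparent convergence.

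**Centre (secondary).** With an Innsbruck share s of patients and an Aachen share q of controls, neither given in the article, a Vienna-only contrast has a standard error larger by √[1/(60(1 − s)) + 1/(60(1 − q))] / √(2/60).

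- s = 0.1, q = 0.25: √(0.0407/0.0333) = 1.11.
- s = 0.3, q = 0.75: √(0.0905/0.0333) = 1.65.

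**The case against.** Several points on the other side have force.

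- **The routes may hardly differ in practice.** The 24 h is a usual time and not a cap, and the 48 h reads as an upper limit. Holding times could overlap widely. This stands: h may be small, and the article does not allow it to be estimated.
- **The switch is neither universal nor immediate.** Some patients may still be inpatients at T_6, and the change from T_A to T_D stays on one route. This stands and narrows the point to the admission contrast and the change to T_6 and T_12.
- **The comparison is descriptive.** No confirmatory patient-control test is planned. True, but a shifted interval misleads whether or not a test accompanies it.

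Three stronger readings are tempting, and the documents do not support them. The first is that handling must push patients towards controls. The article gives no sign for the effect, and the third case above shows the opposite result. The second is that the treatment comparison is compromised. Both arms follow the same instructions, so the switch cancels between them. The third is that the different centres invalidate the control comparison, or oblige the trial to make a Vienna-only contrast the main one. Vienna is the main source of patients and also supplies controls, so the overlap is partial but real. Site adjustment is a matter the analysis plan may already settle.

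**Conclusion.** The point holds for stool handling. The plan as written ties the collection route to group at admission and to visit within patients, so the whole of any route effect enters the admission contrast. The same effect, reduced by the share of patients still in hospital at T_6, enters the change to follow-up relative to controls. Under the assumptions above, an effect of 0.2 to 0.5 SD would make a 95% interval exclude zero in roughly 20% to 78% of trials with no true difference or change. These are illustrations, because no effect size is available from the documents. The effect can imitate normalisation or mask it.

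The primary endpoint, the probiotics-placebo microbiome comparison and the change from admission to discharge are not affected by the switch. The centre imbalance is a lesser matter that calls for a sensitivity analysis.

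**What to change.** 1. Record the collection time and the freezing time of every stool sample, in patients and controls. If clock times are already logged, this step is done.
2. Ask home collectors to sample close enough to the visit that the same maximum time to freezing, for example 24 h, applies to all samples. State that the clock starts at collection.
3. Include time to freezing as a covariate in the patient-control microbiome models.
4. Repeat the patient-control comparison with only those samples frozen within 24 h.
5. Report a Vienna-only patient-control contrast as a sensitivity analysis, not as the main comparison.

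The cost is one logged time per sample, some rescheduled home collections and a wider interval in the restricted analysis. The Vienna-only contrast has a standard error about 1.1 to 1.65 times larger under the assumed centre shares. The patient consent statement suggests that enrolment may have begun. If so, changing the collection window adds a break in procedure by calendar time, and the logged times should be used to check for it. The covariate adjusts for holding time only; other differences between home and ward collection remain, which is why aligning the window comes before modelling.

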**FIGURE 1 erv2876-fig-0001:**
[figure not shown]
Study design of the present study. Blinded: name of study sites

### Inclusion and exclusion criteria

2.4

Inpatients aged 13–19 years, who are admitted to the Eating Disorders Unit at the Departments of Child and Adolescent Psychiatry, Medical University Vienna and Medical University of Innsbruck with the diagnosis of AN (307.1) or atypical AN (307.59) according to DSM‐5 will be eligible for the study. Written informed consent from participants and one legal representative, if patients are younger than 18 years, are required. Patients with comorbid disorders including organic brain disease, psychotic or bipolar disorder, substance use disorder, serious self‐injury, diabetes, those with insufficient knowledge of the German language, and those who used antibiotics during the last 6 weeks will be excluded. Further exclusion criteria are pregnancy and organic disorders with impact on the gastrointestinal tract (e.g. inflammatory bowel disease, coeliac disease). Previous operations on the gastrointestinal tract will be evaluated in the individual case. The same inclusion and exclusion criteria apply to the healthy controls; however, they have to be absent from any current diagnosed psychiatric disorder and current or lifetime eating disorder.

### Procedure

2.5

Trial participants who are eligible will be informed about the study procedures by the research staff and written informed consent will be obtained separately from the participants and one of the legal representatives, when the patients are younger than 18 years. The participants and the legal representatives are asked whether they consent to the storage and further analyses of blood and stool samples even in case of drop out from the study. After informed consent was obtained, patients will be randomized to the probiotics or placebo conditions (see section *Randomisation*) and baseline assessment (T_A_) of outcome variables including neuropsychological measures, eating disorder related and other psychopathology, collection of blood and stool samples will be performed (see Section 2.8). As soon as baseline assessments are finished, the intervention (administration of probiotics or placebo) is stared (see Section 2.6). Assessments will be repeated at discharge (T_D_, only in patients with AN), 6 months after baseline (post‐intervention, T_6_) and at 12‐month follow‐up (T_12_).

The trial procedures were approved by the local Research Ethics Committee at the Medical University of Vienna (reference number 2226/2018; 30 April 2019) and the Ethics Committee at the Medical University of Innsbruck (reference number 1118/2019; 21 August 2019) and will be carried out in accordance with the Declaration of Helsinki. The study was registered at the German Clinical Trials Register (DRKS00017726, 30 August 2019).

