### Measures and instruments

2.8

In order to evaluate the effect of probiotic administration in patients with AN, various measures are obtained at baseline, discharge, post‐intervention and 12‐month follow‐up. Assessments at discharge are omitted if the post‐intervention assessment (6 months after baseline) is scheduled 2 weeks before or one month after discharge. A complete list of all measures and instruments used in patients and healthy controls including the time points when they are assessed is provided in Table 1.

**TABLE 1 erv2876-tbl-0001:** Summary of measures and instruments used in the present study

Instrument/measure	Domain/aim	Time point^a^			
		T_A_	T_D_	T_6_	T_12_
Sociodemographic questionnaire	Key sociodemographic and clinical data	x	–	–	–
Body‐mass‐index (BMI)	Weight/weight gain	x	x	x	x
Eating disorder examination interview (EDE; Cooper & Fairburn, 1987)^b^	Eating disorder diagnosis and symptomatology	x	x	x	x
Eating disorder examination questionnaire (EDE‐Q; Hilbert et al., 2007)	Eating disorder symptomatology (self‐report)	x	x	x	x
Eating disorder inventory‐2 (EDI‐2; Garner, 1991)	Eating disorder symptomatology	x	x	x	x
MINI interview/MINI‐KID interview (Sheehan et al., 1998)	Psychiatric comorbidity	x			
Beck depression inventory‐II short version (Beck et al., 2006)	Level of depression	x	x	x	x
State‐trait anxiety inventory (state part only) (Spielberger, 2010)	Level of anxiety	x	x	x	x
Yale‐brown obsessive compulsive scale (Y‐BOCS; Goodman et al., 1989)	Obsessive compulsive thoughts and behaviours (self‐report and expert rating)	x	x	x	x
Social responsiveness scale (SRS) (Bölte & Poustka, 2007)^b^	Autistic traits (parent report)	x	‐	x	x
Gastrointestinal complaints questionnaire (Cuntz & Hiller, 1998)	Gastrointestinal complaints	x	x	x	x
Iowa gambling task (IGT; Bechara et al., 1994)	Executive functioning (decision‐making processes)	x	‐	x	x
Probabilistic reversal learning task (PRLT; Cools et al., 2009)	Cognitive flexibility	x	‐	x	x
Food and non‐food related Go/No go task (Rosval et al., 2006)	Sustained attention and response control	x	‐	x	x
UPPS‐P impulsive behaviour scale (negative urgency‐scale only) (Whiteside & Lynam, 2001)	Level of emotion‐driven impulsiveness	x	‐	x	x
BIS/BAS questionnaire (Carver & White, 1994)	Sensitivity for reward and punishment	x	‐	x	x
Wechsler intelligence test (two subtests: Matrices and vocabulary) WISC‐V (Petermann, 2017) or WAIS‐IV (Petermann, 2012)	Intelligence	‐	‐	x	‐

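### Section 2.5 allocates patients before the baseline assessment while the product starts only after it, so a probiotic-arm patient lost in between counts untreated in the ITT analysis: a small, avoidable loss of power

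*Protocol article*

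**What the plan says.** Section 2.5 (Procedure) of the protocol article opens with patients whose eligibility is already settled: "Trial participants who are eligible will be informed about the study procedures by the research staff". It continues: "After informed consent was obtained, patients will be randomized to the probiotics or placebo conditions", and in the same sentence says that T_A will be performed. The product follows: "As soon as baseline assessments are finished", the intervention begins. The events are thus named in the order consent, randomisation, T_A, first dose.

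Section 2.13 defines the primary analysis as intention to treat, "including all randomized patients irrespective of the amount of treatment actually received". BMI is to be sought at 6 and 12 months even from patients who stop treatment. A per-protocol analysis is planned as a sensitivity analysis.

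Section 2.4 lists the exclusions: "Patients with comorbid disorders including organic brain disease, psychotic or bipolar disorder, substance use disorder, serious self‐injury, diabetes", among others. Table 1 schedules the MINI/MINI-KID interview, whose domain is given as "Psychiatric comorbidity", at T_A only. The eating disorder interview is also done at T_A, and at the later visits.

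Under section 2.7 the institute in Kiel allocates centrally and tells the site which medication number to use. The stratifiers are centre and BMI percentile at admission.

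**The concern.** Any interval between allocation and first dose is one in which a patient can be lost to treatment but not to the analysis set. Here the interval contains the whole of T_A: interviews, neuropsychological tests, blood, a stool sample with food and activity recorded over the preceding 48 h, and imaging in 30 of the patients. Someone may withdraw during this work. One of the interviews may also bring to light a disorder that section 2.4 excludes. In either case the patient has been allocated and belongs to the primary analysis without having taken a sachet.

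In the probiotic arm this has one of two effects. If BMI is still measured at later visits, the patient contributes an untreated outcome to the probiotic mean and pulls the difference towards zero. If there is no later BMI, the patient adds little or nothing to the repeated-measures model, and the cost is precision. With 30 patients per arm, each such patient is 3.3% of the arm. The loss is avoidable, because nothing in the article requires allocation before T_A.

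**Working it through.** **Inputs.** From section 2.12: d = 0.75 for change in BMI, two-sided t-test, alpha 0.10, 80% power, 24 per group needed, about 10% dropout, 30 per group recruited. From section 2.7: 1:1 allocation. Not in the article: the share f of the probiotic arm that is allocated but never starts. It is assumed here and varied from 0 to 20%.

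**Formula.** Power of the two-sample t-test with n per group comes from the noncentral t distribution with 2n − 2 degrees of freedom and noncentrality d·√(n/2). For n = 30 and d = 0.75 the noncentrality is 0.75 × √15 = 2.905, and the critical value on 58 degrees of freedom is 1.672.

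**Reproducing the plan's figures.** The smallest n for 80% power is 23 (24 stated; power at 24 is 82.0%). Power at 30 per group is 89.0% for d = 0.75 (88% stated), 98.6% for d = 1.0 (98% stated) and 80.0% for d = 0.65 (80% stated). All agree closely. Allowing for dropout, 24/(1 − 0.10) = 26.7, so 27 per group would do and 30 leaves three spare.

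**Case 1: untreated but measured.** Assume these patients have the placebo outcome and the SD is unchanged. Then d_eff = 0.75 × (1 − f).

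| Untreated share of probiotic arm | d_eff | Power, 30 per group | Power, 27 per group |
|---|---|---|---|
| 0 | 0.750 | 89.0% | 85.9% |
| 1/30 | 0.725 | 87.1% | 83.7% |
| 2/30 | 0.700 | 85.0% | 81.4% |
| 3/30 (10%) | 0.675 | 82.6% | 78.9% |
| 20% | 0.600 | 74.3% | 70.2% |

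The 27-per-group column applies the plan's own 10% dropout in addition. There, 10% untreated is the first row to fall below 80%.

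**Case 2: no BMI after baseline.** Here d stays at 0.75 and n falls. If the same number is lost in both arms, power is 88.0% at 29 per group, 85.9% at 27 and 82.0% at 24. This costs less than dilution by the same share: 85.9% against 82.6% at 10%.

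**Untreated placebo patients.** If placebo is inert, an untreated patient in that arm has the same expected outcome as a treated one, so d does not change.

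**The case against.** The strongest reply is that eligibility is settled beforehand. Section 2.5 speaks of participants who are already eligible when they are informed, and section 2.4 ties entry to an admission diagnosis in a specialist unit. A reader might infer from Table 1 that the eating disorder interview and the MINI are the eligibility screen and that screening therefore happens after allocation. The article does not say so: section 2.5 describes T_A as an assessment of outcome variables, and section 2.8.2 lists both interviews under the secondary outcome measures. This part of the objection stands. What remains is that a structured interview held only at T_A could reveal an exclusion that was missed earlier. Early withdrawal needs no such inference.

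Several other strong readings are tempting and go beyond the text:

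- That allocation precedes the first dose by days. Randomisation and T_A are joined by a plain *and*, and no interval is given. The 48 h recording suggests about two days only if all of it falls after allocation.
- That every patient lost in the window dilutes the effect. Only untreated probiotic-arm patients with later BMI do.
- That starting antibiotics in the window leaves a patient untreated. Section 2.4 excludes antibiotic use in the previous 6 weeks, but nothing says that later use prevents dosing.
- That each loss breaks a randomisation block. A patient kept in the ITT set leaves the block intact there, and a patient lost altogether affects it no differently from any later dropout.

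It is also fair to say that these are supervised inpatients, that nothing suggests heavy loss before the first dose, and that three spare patients per arm absorb some of it. The per-protocol analysis helps interpretation but does not restore the power of the primary comparison. The BMI covariate and the stratifying percentile are taken at admission, so an incomplete T_A does not remove them from the primary model.

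**Conclusion.** The point holds as a small matter of efficiency. On the order that section 2.5 gives, and with the ITT set of section 2.13, a probiotic-arm patient lost between allocation and first dose counts untreated. With 30 per group the cost is about 2 power points for one such patient (89.0% to 87.1%), 4 for two (85.0%) and just over 6 for three (82.6%). Power drops below the planned 80% when 10% are untreated and only 27 per group are analysed (78.9%).

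These figures rest on an assumed number of untreated patients, on their having the placebo outcome, on the plan's d of 0.75, and on a t-test standing in for the mixed model. The stated order is clear enough to act on; how many patients would be affected is unknown.

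A reader might take this as a bias in the trial result. The documents do not support that: allocation is central and blinded, and dilution works against the product in a superiority comparison. No stated figure is wrong and no two sections contradict each other.

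**What to change.** Reorder section 2.5 as follows: consent; T_A, including the eating disorder interview and the MINI/MINI-KID; confirmation of eligibility; then the request to the randomising institute for the medication number, immediately before the first dose. This is feasible because centre and admission BMI percentile are known by then and the institute already issues numbers patient by patient. Blinding, stratification and the ITT principle are unchanged. Patients already randomised stay in the ITT set.

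If sites already complete T_A before requesting a number, one clarifying sentence is enough.

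The cost is one sentence in the protocol or a site instruction, with no extra visits, patients or measurements. The only downside is that the number is requested slightly later.
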